### **Interventions and Duration**

1. Ovarian hyperstimulation (10 to 30 days): All subjects will receive controlled ovarian hyperstimulation with gonadotropin releasing hormone (GnRH) agonist long or short protocol or GnRH antagonist protocol as per physician preference.
2. Oocyte retrieval, ICSI and embryo culture (5 days): Oocyte retrieval will be performed 34 to 36 hours after oocyte maturation trigger by hCG, GnRHa, or dual trigger. Intracytoplasmic sperm injection (ICSI) will be applied for all included subjects. On the day 5 of embryo culture, women with 3 or more blastocysts will be randomized in a 1:1 ratio into one of two groups: the PGS or the non-PGS group.
3. Embryo biopsy, vitrification and NGS test: Subjects in both groups will have all their embryos frozen and undergo single frozen blastocyst transfer. Subjects assigned to the PGS group will have 3 blastocysts biopsied on day 5 and tested by NGS. Subjects assigned to the non-PGS group will have 3 day-5 blastocysts selected for the first 3 transfers. In both groups, the best blastocysts by morphologic criteria will be selected for NGS or transfer. Assisted hatching will not be performed.
4. A recovery period after ovarian stimulation of 6-10 weeks to allow, shedding of the endometrial lining, decline of steroid hormones, and restoration of normal ovarian function: Endometrial preparation will be started at the second or third menses cycle after oocyte retrieval. Both natural ovulation cycle and artificial regimen will be allowed for endometrial preparation.
5. Pregnancy evaluation and follow-up (2 weeks to 10 months): All pregnancies will be followed up till termination or delivery.
6. Outcome of subsequent transfers (12-21 months): If live birth isn't achieved by the initial transfer and there are euploid embryos in the PGS group or morphologically transferrable embryos in the IVF group, subsequent single embryo transfer(s) will be performed (up to 3 or up to one year after randomization). The cumulative live birth rate will be counted after transfers of all euploids in the PGS group and 3 blastocysts in the IVF group or all transfers within 1 year after randomization in both groups.

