## 4.3 Study Enrollment Procedures

4.3.1 Recruitment: Potential subjects who meet the preliminary screening criteria (age 20 to 37 years and undergoing their first cycle of IVF) after opting for IVF will be referred to the local investigator before the start of ovarian stimulation by other physicians at study sites. A copy of the informed consent will be given to the interested subjects to read before meeting with local investigators.

4.3.2 Screening log: A standard screening log will be kept by local investigators in each study site to record all the subjects screened (subjects committing to IVF and offered the study), reasons for ineligibility and for nonparticipation of eligible subjects. The local screening log will be reported to DCC monthly.

4.3.3 Consent procedure: The local investigator will explain this trial in detail to potential subjects and their partners and answer any questions raised by them prior to signing the written informed consent to participate in the study. At the start of ovarian stimulation, written consent will be obtained from both the female subject and her partner. A copy of the signed written informed consent form will be given to the subjects.

4.3.4 Assignment: On day 5 of embryo culture, eligible subjects will be randomized via an online central randomization system. The assignment will be informed to subjects and their physicians.

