## 5.2 Handling of Study Interventions

Embryo biopsy and NGS will be performed at local sites.

- 1) Embryo biopsy should be completed by the same embryologist at each study site, who has more than 3-years experience to minimize damage on embryos, and different micromanipulators and different laser frequency used in the participating IVF centers are allowed. Biopsy should be performed on Day 5 of embryo culture when blastocysts reach score 4BC or better and fully expand. The biopsy site should be right opposite to the ICM and only 3-5 herniating TE cells will be aspirated. After the operation, survival

03/07/2017

of the embryo is regarded as a success and operation time should be recorded. Patient's name, the medical record number and embryo number should be clearly marked to ensure the consistency.

- 2) Different NGS platforms (*Illumina MiSeq/NextSeq550 or Life Tech PGM/Proton*) applied in different IVF centers are allowed. This reflects current practice where different platforms are used. The resolution value is defined as 4Mb. For laboratory environment and facilities, reagent preparation district, WGA preparation district, library preparation district, product purification district and sequencing district should be separated to prevent contamination and buffering area should be set between the adjacent districts. For laboratory technicians, professional training and technical competence is required. For WGA, first, sample-positive control and negative control are necessary; Second, concentration of products detected using Qubit assay should be no less than 20ng/  $\mu$ l, and those of negative control should be less than 10ng/  $\mu$ l; Third, two technicians are needed to prevent confusion when to transfer samples between tubes. For library preparation, the concentration should be more than 0.5 ng/  $\mu$ l and the volume should be no less than 20  $\mu$ l. For sequencing results, the quality control standard of different platforms should be established and complied with. For example, based on Proton of Life Tech, the loading rate should be more than 60%, polyclone rate no more than 40%, low quality rate no more than 30%, and reads counts of each sample larger than 1M. In the last, all operations should be completed by two technicians together in the lab and auditors should audit the original data and check the sequencing report.

This is an open-label unblinded trial because it is not possible to mask the embryo biopsy.

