### 5.3 Concomitant Interventions

#### 5.3.1 Required Interventions

Participants will receive controlled ovarian hyperstimulation (COH) with agonist via a long or short protocol, or an antagonist protocol, HCG or GnRH $\alpha$  trigger final oocyte maturation, and standard ultrasound guided oocyte retrieval, ICSI procedure and embryo culture according to clinical routine in different study sites. An elective freeze-all strategy and single frozen embryo transfers will be employed. The transfer order in the PGS group will be decided by both NGS results and embryo morphologic score, while transfer order in the non-PGS group will be decided by morphologic score alone. The endometrium for FET will be prepared either through a natural ovulation cycle or artificial cycle. The choice of which will be up to the site investigator. Luteal phase support will be administrated according to the routine in different sites. A pregnancy test will be performed 2 weeks after embryo transfer. If pregnancy is confirmed, luteal phase support will be continued till 10 weeks of gestation. The follow-up will continue until termination or delivery.

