#### 1) COH and oocyte retrieval:

GnRH agonist long or short or antagonist protocol will be allowed for ovarian stimulation at the discretion of local investigators. The long protocol starts with GnRH agonist (triptorelin) administrated in the mid luteal phase of the previous cycle and gonadotropin is initiated when satisfactory pituitary desensitization is achieved. The short protocol starts with administration of GnRH agonist on day 2 or 3 of the menses and gonadotropin 2 days later. The antagonist protocol starts with admin-

03/07/2017

istration of r-FSH on day 2 or 3 of the menses cycle and combines with antagonist (cetorelix or ganirelix) on day 5 or 6 after gonadotropin initiation or when dominant follicles  $\geq 12$  mm mean diameter, and continues until the trigger day. Then the r-FSH dosage and addition of other drugs (HMG, recombinant growth hormone et al.) will be adjusted in the light of follicle growth monitored by transvaginal ultrasound and serum steroid levels.

HCG and/or GnRHa trigger for final oocyte maturation will be administrated when at least two follicles  $\geq 18$  mm mean diameter. Transvaginal ultrasound guided oocyte retrieval will be performed 34 to 36 hours after trigger.

2) ICSI procedure, embryo culture, and embryo score

The oocytes will be inseminated approximately 4~6 hours after follicular aspiration. Fertilization will be achieved by ICSI in all subjects. All embryos will be cultured in the sequential media to blastocyst stage. Embryo score by Gardner criteria. Subjects with 3 or more blastocysts with score 4BC or better on day 5 will be randomized to PGS or non-PGS group.

3) Embryo vitrification

All embryos will be frozen and no fresh embryo will be transferred.

4) Endometrial preparation, embryo transfer and luteal phase support

Endometrium preparation will performed with either a natural ovulation cycle or an artificial regimen depending on the choice of the site investigators after the second spontaneous menses following oocyte retrieval. A single frozen blastocyst will be transferred each time. Luteal phase support will be added according to local routine. The procedure will be completed under transabdominal ultrasound guidance (with full bladder). All medications used for endometrial preparation and luteal phase support will be documented.

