### 6.2.3 Intervention Discontinuation Evaluations

After randomization, further participation in the study will be discontinued in the following situations: a) no euploid embryo is obtained in patients assigned to the PGS group after NGS test; b) Subjects who run out of the protocol-specified embryos; c) Subjects who do not complete transfers of the protocol-specified embryos within 1 year after randomization. Subjects who conceive will be followed to the termination of the pregnancy.

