#### 9.5 Data Analyses

The primary analysis will be performed in accordance with the principle of intent-to-treat. Continuous variables will be described as mean  $\pm$  standard deviation for the normally distributed variables and as median and range for the non-normally distributed variables. Category variables will be presented as frequency and percentage. The differences in the cumulative live birth rate in the two treatment arms will be compared by absolute risk difference and its 95% confidence interval (CI). The relative risk and its 95% CI will also be calculated. Non-superiority of PGS to IVF will be considered to be established if the upper limit of the 95% CI of absolute risk difference was shown to lie below the non-superiority margin of 7%.

The differences in the secondary outcomes such as rate of Good Birth Outcome, cumulative pregnancy rate, cumulative pregnancy loss rate, multiple pregnancy rate obstetric and neonatal complications will be tested by Person chi-square analyses. The absolute difference and 95%CI as well as relative risk and 95% CI will also be calculated. The difference between duration of pregnancy, birth weight and times of embryo transfer will be tested by student t test and non-parameter test if necessary.

The tertiary outcomes such as the rates of pregnancy, pregnancy loss and live birth after the first transfer will be analyzed with Pearson chi-square test. Cost-effectiveness analysis will be done by decision analytic model with TreeAge Pro 2014 (2014 Version; TreeAge

software). Cost effectiveness is defined as an incremental cost effectiveness ratio (ICER). The ICER for live birth was calculated as the difference in cost between two treatment groups divided by the difference in live birth rates between the two groups. The secondary analysis will be performed according to per-protocol analyses. The primary and secondary outcomes will be compared according to actual treatment that subjects received and among subjects who complete embryo transfer(s).

Subgroup analyses will be performed according to different stimulation protocol (e.g. agonist long, agonist short, and antagonist protocol), different endometrial preparation protocol for FET (e.g. natural ovulation cycle and artificial cycle), age groups (e.g. 20~30 group, 30~35 group and >35 group), with or without history of recurrent spontaneous abortion.

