**Final statistical analysis**

Given the possibility of false positive and the decision of not transferring mosaic embryos which are probably to develop into live birth, we hypothesized that the cumulative live birth rate after the transfer of PGT-A-selected euploid blastocysts is not clinically better than that after serially transferring all the 3 untested blastocysts. This study was therefore designed as a non-superiority study. It was estimated the cumulative live birth rate after 3 single embryo transfers was 65% in each group. To be 80% certain that the upper limit of a one-sided 95% confidence interval (CI) would exclude a difference in favor of the PGT-A group by more than 7%, 575 patients were required in each group. In consideration of 5% drop-out rate, a total of 1,208 patients were needed.

Continuous baseline characteristics of PGT-A and IVF groups were represented as means  $\pm$  SD, and between-group differences were compared by Wilcoxon rank-sum test. Categorical variables were represented as frequencies and percentages, and compared by chi-square test. Fisher's exact test was performed for the number of frequencies less than five. Non-superiority test was used to evaluate the absolute rate differences with a two-sided 90% CI for the primary hypothesis only. Other categorical variables were analyzed by estimation of absolute rate differences and relative rates with a two-sided test. Kaplan-Meier curves were used for the time to live birth. We also conducted secondary analyses based on actual treatment that the patients received, the initial, secondary and third embryo transfer in PGT-A and IVF groups. Subgroup analyses were performed according to different endometrial preparation protocol for frozen embryo transfer and age groups. Two-sided P value of  $<0.05$  were considered significant. All analyses were performed using SAS software (version 9.4, SAS Institute).

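### Endometrial preparation is a post-randomisation subgroup, undefined for women without a transfer; if it is used to compare cumulative live birth, it structurally favours PGS

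*Combined protocol and SAP*

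**What the plan says.** Section 9.5 lists four subgroup factors: stimulation protocol, "different endometrial preparation protocol for FET (e.g. natural ovulation cycle and artificial cycle", age group, and history of recurrent spontaneous abortion. It does not treat the second differently from the others. The Final statistical analysis section keeps it: "Subgroup analyses were performed according to different endometrial preparation protocol for frozen embryo transfer and age groups". That section does not name stimulation protocol or abortion history. Neither place gives the subgroup's outcome or denominator, a rule for women with no transfer, or a rule for a regimen that differs between transfers.

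The order of events is spread over several sections:

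- Section 4.3: "On day 5 of embryo culture, eligible subjects will be randomized via an online central randomization system". The same section has the allocation disclosed to subjects and physicians.
- Section 5.2: "This is an open-label unblinded trial because it is not possible to mask the embryo biopsy".
- Synopsis, Interventions and Duration: "Endometrial preparation will be started at the second or third menses cycle after oocyte retrieval".
- Section 5.3.1, on natural versus artificial cycle: "The choice of which will be up to the site investigator". Its item on endometrial preparation repeats this: "Endometrium preparation will performed with either a natural ovulation cycle or an artificial regimen depending on the choice of the site investigators".
- Section 6.2.2 records the regimen used.
- Section 6.2.3 ends participation when "no euploid embryo is obtained in patients assigned to the PGS group after NGS test".
- Section 9.2.1 divides the women with a live birth by all women randomised to the group.

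**The concern.** A subgroup comparison keeps the protection of randomisation only if membership is settled before allocation, or cannot be influenced by it. Here membership is settled weeks later, by someone who knows the arm and may know the sequencing result. It also requires that a transfer be prepared.

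That requirement does not act equally on the two arms. Every IVF woman enters with at least three blastocysts eligible for transfer. A PGS woman whose three tested embryos yield nothing transferable has no study transfer, no regimen and no possible study live birth. She is a certain non-success in the primary analysis and belongs to neither regimen stratum. Comparing the arms within strata therefore removes a set of known failures from PGS only.

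At stake is the reading of a secondary table. In a trial that asks whether PGS is better, a positive difference within a regimen could be taken to mean that PGS works under that preparation, although none of it need be a treatment effect.

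**Working it through.** **Inputs.** Cumulative live birth 65% in each group (Synopsis, Sample Size and Population). Three blastocysts sequenced (5.1). Euploidy about 60% (2.1). Alternative rates from 2.2: aneuploidy of about 34%, 36.1% and 44.9%, hence euploidy of about 66%, 63.9% and 55.1%; and 40% to 56% euploid among top-scoring blastocysts. Mosaics are not transferred, but embryos with failed amplification are (5.1.3).

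**The plan's own figure.** With one-sided 5% alpha, 80% power, 65% in both groups and a 7-point margin, n = (1.645 + 0.842)² × 2 × 0.65 × 0.35 / 0.07² = 6.183 × 0.455 / 0.0049 = 574.1, so 575 per group as stated. Then 1150 × 1.05 = 1207.5, so 1208 in total and 604 per arm.

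**Step 1: share of PGS women with no regimen for lack of a euploid embryo.** With independent embryos and euploidy e, this is (1 − e)³. At e = 0.60 it is 0.4³ = 0.064, or 0.064 × 604 ≈ 39 women.

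**Step 2: PGS rate among the rest.** The excluded women have no live births, so the numerator is unchanged and the rate is 0.65 / (1 − (1 − e)³). At e = 0.60 it is 0.65 / 0.936 = 69.4%. IVF stays at 65%.

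| Euploidy | PGS women excluded | PGS rate in pooled strata | Apparent difference |
|---|---|---|---|
| 66% | 3.9% | 67.7% | +2.7 points |
| 63.9% | 4.7% | 68.2% | +3.2 points |
| 60% | 6.4% | 69.4% | +4.4 points |
| 56% | 8.5% | 71.1% | +6.1 points |
| 55.1% | 9.1% | 71.5% | +6.5 points |
| 40% | 21.6% | 82.9% | +17.9 points |

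The last row is an outer bound. It holds the PGS arm at 65% overall, which would require 82.9% among women with a euploid embryo. With all randomised women in the denominator, the difference is 0 in every row.

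**Step 3: sensitivity at 60% euploidy (all three rates assumed).**

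- Amplification failure at rate a per embryo, with those embryos transferred, gives an excluded share of ((1 − a) × 0.4)³. At a = 2% this is 6.0% (+4.2 points); at 5% it is 5.5% (+3.8 points).
- Correlated ploidy within a woman (beta-binomial) raises the share to 9.4% at a correlation of 0.1 (+6.7 points) and 12.5% at 0.2 (+9.3 points).
- If 5% of women in both arms also miss transfer for other reasons and have no live birth, the difference is 0.65 / (0.95 × 0.936) − 0.65 / 0.95 = 73.1% − 68.4% = +4.7 points. A common loss does not cancel the asymmetry.

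**What cannot be computed.** All these figures pool the two regimens. The difference within each depends on how women in each arm are spread over regimens, which the documents do not give.

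**The case against.** The strongest reply is that the plan never says the subgroup is cumulative live birth among women with a regimen. Section 9.5 also plans first-transfer outcomes, and the Final statistical analysis reports the first, second and third transfers. Per transfer, a regimen is well defined, and the difficulty of tying one cumulative outcome to one regimen disappears. This stands, so the bias is conditional on the endpoint and denominator. It does not remove selection on reaching transfer, which remains in any comparison limited to women who had one.

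Second, IVF women can also miss a transfer, through drop-out, the one-year limit, or loss of all study embryos at thaw. That is correct: the point is an additional exclusion in the PGS arm, not an exclusion that only PGS has.

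Third, a reader might infer that investigators chose the regimen according to arm or sequencing result, or that this choice favours PGS. The documents show only that they could have known both. Randomisation was stratified by site, and the choice may largely reflect site practice. Any bias from an arm-aware choice has unknown direction. Likewise, switching regimen between transfers is not ruled out, but it is not stated to occur.

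Fourth, it is tempting to set +4.4 points against the 7-point margin. That margin applies only to the overall primary comparison; no subgroup is tested against it.

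**Conclusion.** The point holds in conditional form. Endometrial preparation is a post-randomisation variable, undefined for women without a study transfer, and the plan lists it with baseline factors without a caveat. If it is used to compare cumulative live birth among women with a recorded regimen, the exclusion of PGS women with no euploid embryo pushes the estimate toward PGS: about +4.4 points under equal true rates at 60% euploidy, +2.7 at 66% and +6.1 at 56%, slightly less when amplification failures are transferred. This rests on three embryos tested, independence between a woman's embryos, 65% in both arms, and an inferred denominator.

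A reader might go further and conclude that the trial's main result is compromised, or that each stratum is shifted by the pooled amount. Neither follows. The primary analysis counts all randomised women and is unaffected, and the split between strata is unknown. Nor does the absence of two planned subgroups from the Final statistical analysis show anything about this one; it is a separate reporting matter.

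**What to change.** Do not use the regimen actually received as a subgroup for between-arm comparison of cumulative outcomes. Report it descriptively, per transfer and by arm, labelled as post-randomisation.

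Limit between-arm subgroups to the planned factors fixed before randomisation: age, stimulation protocol and history of recurrent spontaneous abortion. Keep all randomised women in the denominator, and give the treatment-by-subgroup interaction estimate with its confidence interval.

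The cost is wording in the analysis plan, and one planned subgroup table becomes descriptive only. No change to treatment is involved.

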## 10 DATA COLLECTION, SITE MONITORING, AND ADVERSE EXPERIENCE REPORTING

### 10.1 Records to Be Kept

The baseline characteristics of subject, outcome of ovarian stimulation and in-vitro fertilization, and pregnancy outcome will be collected with standard case report form (CRF) by local investigators. The hard copy of CRF will be kept in study site in a study-specific cabinet with lock. For the purpose of managing the data, monitoring the process and promoting the transparency of the study, a web based database, Clinical Trial Electronic Case Record Form (eCRF system) (<http://www.clinicaltrialecrf.org>), will be used to record and deposit the patients' data and results. The collected data will be input into this online database which can only be accessed by authorized personnel.

